**Fig. 3 Fig3:**
[figure not shown]
Schedule of enrolment, interventions, and assessments

### ⑦ Statistical analysis

#### Evaluating the effectiveness of interventions

Quantitative data will be analyzed using STATA according to the principles of intention-to-treat analysis. This study will use t-tests, chi-square tests, and hierarchical generalized linear models to compare the differences in outcomes between the intervention and control groups. For outcome indicators measured at the same time point (e.g., at one month after baseline), t-tests and chi-square tests will be used to compare continuous variables (e.g., level of decisional conflict) and categorical variables (e.g., mental health service utilization), respectively. In contrast, for outcome indicators (e.g., depressive symptoms) that are repeatedly measured at different time points throughout the study period, hierarchical generalized linear models will be used to estimate fixed effects of treatment factors and individual-level random effects.

In addition, this study will use causal mediation analysis to estimate how the levels of SDM affect multiple outcome indicators of patients in the intervention group and the control group, using whether they belong to the intervention or control group as an instrumental variable. Causal mediation effects can be estimated by regression models, depending on the type of exposure, mediator, and outcome variables (whether dichotomous or continuous) and whether the mediating variable interacts with the exposure variable [38]. Analysis of causal mediating effects can also be combined with instrumental variables [39] to analyze the mechanisms by which the levels of SDM itself contribute to multiple patient outcomes.

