**Control variables**		
	Decision-making preferences	Decision-making preferences will be measured by the Control Preference Scale, which is commonly used to measure patients’ willingness preferences to participate in healthcare decision-making. The scale consists of 5 entries that can classify patients into 3 types: active decision makers, negative decision makers, and shared decision makers.
	Mental health literacy and stigma	The Multicomponent Mental Health Literacy Measure (MMHLM), which is commonly used internationally, is applied in this study to measure maternal mental health literacy and stigma. The 22-item MMHLM, which contains three dimensions of knowledge, beliefs, and resources, has good reliability and validity, is suitable for assessing mental literacy in adult populations, and is also a good predictor of mental health service utilization behavior. The Chinese version of the questionnaire has been tested for reliability and validity in a domestic population.

**Baseline Survey**: After obtaining informed consent, a member of the research team will conduct a baseline survey. This survey will include basic maternal personal information (e.g., age, education, marital status, family health history, health insurance), level of decisional conflict, history of mental health service utilization, mental health literacy and stigma, and decisional preferences. Among them, basic demographic and health information (e.g., family health history) will be compared with electronic health records for confirmation.**Follow-Up Survey**: Follow-up surveys will be conducted at one, three, and six months after baseline. These surveys will include measures of shared decision-making (at one month only), decisional conflict, depressive symptoms, mental health service utilization, and associated costs. The primary outcome of this study is the level of decisional conflict one month after baseline.

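### The one-month primary comparison is an unadjusted t-test although baseline DCS is collected, and the article's hierarchical-model rule also covers DCS: name one baseline-adjusted primary analysis

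*Protocol article*

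**What the plan says.** The article fixes the primary endpoint clearly. In Measurements (Follow-Up Survey): "The primary outcome of this study is the level of decisional conflict one month after baseline".

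The section on evaluating the effectiveness of interventions gives two rules for choosing the analysis:

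- **Outcomes at one time point**, with one month as the example: "t-tests and chi-square tests will be used to compare continuous variables (e.g., level of decisional conflict) and categorical variables". No covariate is named.
- **Outcomes measured more than once**: "for outcome indicators (e.g., depressive symptoms) that are repeatedly measured at different time points throughout the study period, hierarchical generalized linear models" are planned, to estimate treatment fixed effects and individual random effects.

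The Baseline Survey includes "level of decisional conflict, history of mental health service utilization, mental health literacy and stigma, and decisional preferences", so every woman surveyed has a baseline DCS. For follow-up, "Follow-up surveys will be conducted at one, three, and six months after baseline", and "These surveys will include measures of shared decision-making (at one month only), decisional conflict, depressive symptoms". Only shared decision-making is limited to one month; DCS is collected at all three follow-ups.

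The general principle is: "Quantitative data will be analyzed using STATA according to the principles of intention-to-treat analysis".

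**The concern.** There are two linked issues.

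First, a two-sample t-test on one-month DCS cannot use the baseline value of the same scale, which is usually among the better predictors of the follow-up value. Variation between women that was already present at baseline stays in the error term, and the confidence interval for the primary effect is wider than it needs to be. Spare precision has some value here, because the Discussion accepts that contamination between arms may pull the result towards no difference.

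Second, the two rules overlap. DCS is the example given for the t-test rule, yet it is measured repeatedly and so also falls under the hierarchical-model rule. Mental health service utilization, the example given for the chi-square test, is likewise collected at every follow-up. If the t-test and the model's month-1 estimate disagreed, the text does not say which would stand as the primary result.

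**Working it through.** **Inputs from the Sample size section:** two-sided alpha 0.05 (z = 1.96); z = 0.84 for 80% power; standardised effect d = 0.3; 174 per group before dropout; dropout up to 15%; 410 in total; 1:1 allocation.

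**Input not in the article:** the correlation r between baseline and one-month DCS. I assume a range of 0.1 to 0.7.

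**Step 1. Reproduce the plan's figure.**
n per arm = 2 × (1.96 + 0.84)² / 0.3² = 2 × 7.84 / 0.09 = 174.2, stated as 174.
With dropout: 174 / 0.85 = 204.7, rounded up to 205 per arm, or 410 in total.
Both figures reproduce, and both are for an unadjusted comparison of two means.

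**Step 2. Power of the planned t-test at 174 analysed per arm.**
Expected z = 0.3 × √(174/2) = 2.798. Power = Φ(2.798 − 1.96) = Φ(0.838) = 79.9%. The exact noncentral t calculation gives 79.7%.

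**Step 3. Power after adjusting for baseline DCS.**
Adjustment reduces the residual SD by the factor √(1 − r²), so power = Φ(2.798/√(1 − r²) − 1.96). For r = 0.5: 2.798/0.866 = 3.231, and Φ(1.271) = 89.8%.

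| Assumed r | Power at 174 per arm | Gain over 79.9% (points) | n per arm for 80% power |
|---|---|---|---|
| 0 (no gain) | 79.9% | – | 175 |
| 0.1 | 80.3% | 0.4 | 173 |
| 0.2 | 81.5% | 1.6 | 168 |
| 0.3 | 83.5% | 3.6 | 159 |
| 0.4 | 86.3% | 6.4 | 147 |
| 0.5 | 89.8% | 9.9 | 131 |
| 0.6 | 93.8% | 13.9 | 112 |
| 0.7 | 97.5% | 17.6 | 89 |

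The table uses the normal approximation. With the t distribution the values at r = 0.3, 0.5 and 0.6 are 83.3%, 89.7% and 93.7%. Put another way, 174 women per arm analysed with adjustment carry the information of 174/(1 − r²) analysed by t-test: 191, 232 or 272 per arm at r = 0.3, 0.5 or 0.6.

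**Step 4. Missing one-month values.**
At 15% loss, 410 − 348 = 62 women would have no one-month DCS, and a t-test on observed values would leave them out. A likelihood-based model of all follow-up DCS values would keep those among them who have a three- or six-month DCS, under a missing-at-random assumption. The article does not say how many that would be.

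**The case against.** The other side has a good case on several points.

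- **Power.** The trial was sized for this t-test and the figure reproduces, so nothing is missing from the planned 80%. This stands. The gain also rests on a correlation that the article does not give. A low value is plausible, because a consultation and a treatment decision may fall between the two measurements; at r = 0.1 to 0.2 the gain is only 0.4 to 1.6 points.
- **Intention to treat.** A reader might infer that an unadjusted t-test contradicts the stated intention-to-treat principle. The article does not support this. Comparing women in the arms to which they were randomised is compatible with that principle, and nothing restricts the test to completers. The article is silent on missing one-month DCS, but that is commonly left to the analysis plan and is no fault here.
- **Dropout.** The 15% is described as leaving the study. A woman who leaves before month 1 has no later DCS either, so a model with baseline DCS as a covariate would not recover her. Only women who miss month 1 and return later are kept, and the target of 410 already allows for the loss.
- **Chance imbalance.** Under randomisation the unadjusted difference is unbiased and its standard error already allows for chance imbalance. Adjustment improves precision; it does not repair a bias.
- **The overlapping rules.** The natural reading is a t-test for the one-month endpoint and the hierarchical model for the course over time, since depressive symptoms are the example for the second rule. That is reasonable, but the text does not say it, and by its literal terms the second rule covers DCS.
- **Control variables.** Decision preference and mental health literacy and stigma cannot enter a t-test, but they may enter the other planned models. The covariate list can be left to the analysis plan.

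**Conclusion.** The point holds as an improvement in efficiency and clarity. The planned primary analysis is valid and adequately powered on the article's own assumptions. It leaves unused a baseline measurement that the trial will already have, and it does not say which of two applicable rules governs the primary outcome.

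The benefit at 174 per arm and d = 0.3 runs from almost nothing (80.3% power at r = 0.1) to substantial (89.8% at r = 0.5, 93.8% at r = 0.6). It becomes material from about r = 0.4 to 0.5 upwards. A reader might infer that the trial is underpowered; it is not.

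The calculation assumes a linear relation between baseline and one-month DCS, similar variance in both arms, and baseline DCS recorded before the woman's allocation is known. The text places both the survey and randomisation after consent. The flow and schedule figures, which may give the order, are not shown, so I raise no fault on that.

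**What to change.** In the section on evaluating the effectiveness of interventions, name one primary analysis of DCS at one month, adjusted for baseline DCS. Either form would do:

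- ANCOVA of one-month DCS on arm and baseline DCS; or
- the hierarchical model already planned, fitted to DCS at one, three and six months with baseline DCS, arm, time and arm-by-time, and with the month-1 arm difference as the primary contrast. This form also keeps women who miss month 1 but have a later DCS, under missing-at-random.

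Keep the unadjusted t-test as a supportive analysis, and add one sentence saying that the primary result is the adjusted month-1 difference whatever the other analyses show.

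The cost is a change of wording before the outcome data are examined. It needs no new measurements, no extra participants and no change to the target of 410. It is a free improvement.

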**Patient Decision Aid**: Participants in the intervention group will receive a patient decision aid for PND prior to their clinical consultation. The patient decision aid will be distributed as a paper booklet, similar in size to the educational materials on perinatal mental health that are routinely distributed at the study site. The patient decision aid will support patients to identify their decision-making problems, understand treatment alternatives, and support them to discuss PND screening results and treatment options with maternal care and mental health professionals, and facilitate SDM.**Decision Coaching**: One week after the clinical consultation, the mother will receive a telephone call back from the mental health nurse, during which the nurse will counsel the patient on decision making based on the IP-SDM model. Specific components include identifying decision problems, exchanging evidence-based information, clarifying the patient’s values and preferences, assessing the feasibility of possible treatment modalities, and evaluating preferred options with the patient. The nurse’s decision coaching will also be available to family members if the patient agrees and requires it.**Clinical Consultation**: If patients attend the study site’s mental health clinic and the joint psychological specialist clinic, the clinician will also conduct a shared decision-making process with the attending pregnant and postpartum women, following the steps in the IP-SDM model. This process will also engage the family if the patient agrees and requires it.

Mental health nurses at the study site, as well as physicians in the mental health clinic and joint psychiatric specialist clinic, will receive training on the implementation of the IP-SDM model, including how to use decision aids with patients and how to provide decision support to patients in decision coaching and clinical consultation. In addition to the training, the research team will develop communication scripts prepared in a step-by-step decision-making process to help health care providers deliver standardized interventions and thereby prevent “contamination” of interventions.

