**Primary outcome indicators**		
	Quality of decision-making process	The core indicator of quality of decision-making process is the decisional conflict, i.e. the inner uncertainty of the patient about the treatment option to be chosen during the medical activity. The level of decisional conflict will be measured by the Decisional Conflict Scale (DCS). This scale is the most widely used tool for evaluating decisional conflict and consists of five dimensions: informed, i.e., the extent to which patients understand the potential benefits and risks of the options available to them; value clarification, i.e., the extent to which patients are clear about their values (to measure the benefits and risks); decision support, i.e., the extent to which patients feel supported in their decision; uncertainty, i.e., the extent to which patients are certain about the decision being made; decision validity, which is the patient’s perceived effectiveness, or satisfaction, with the decision. The Chinese version of the scale has also been widely used in studies with good reliability and validity.

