**Secondary outcome indicators**		
	Shared decision-making	Shared decision-making will be measured based on an adapted decision expectancy scale (control preference scale, CPS). This scale was originally used to measure patients’ willingness to participate in health care decision-making. In its adaptation, it can also measure patients’ actual participation in decision making in a given decision situation and can classify patients into three types: active decision makers, negative decision makers, and shared decision makers. This is one of the most commonly used and concise tools for measuring shared decision-making.
	Mental health service utilization	A self-administered questionnaire will be used to investigate whether mothers are diagnosed by a psychiatrist with a mental disorder such as PND and the utilization of subsequent mental health services, including all mental health services such as counseling, psychotherapy, and psychiatric services received by mothers at the study site and other institutions or settings (e.g., number of visits, number of counseling sessions, length of medication, etc.).
	Cost	A self-administered questionnaire will be used to measure the costs associated with maternal mental health service seeking. The self-administered scale will be developed with reference to the Treatment Inventory of Costs in Psychiatric Patients and will consist of: direct medical costs, including the costs of maternal psychiatric services, psychotherapy, counseling, etc. (including maternal and health insurance paid costs); direct non-medical costs, including transportation and accommodation fees for maternity and their companions seeking mental health services; indirect costs, including labor losses such as lost wages for maternity and their companions as a result of seeking mental health services. As the related costs are incurred within six months, no discounting is required. Self-administered questionnaires will also be used to measure the cost of conducting the interprofessional shared decision-making model and subsequent mental health services, including mainly depreciation of fixed assets and staff labor costs, among medical staff and hospital administrators.

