Furthermore, the IP-SDM model aims to increase acceptance of evidence-based mental health services for PND in maternal care settings. In these settings as well as other primary care settings, patients may not seek care for mental health concerns due to stigma or lack of mental health literacy [44]. Additionally, providers may lack the necessary skill sets or time to deliver mental health services [45]. Obstacles at the health system level may include a lack of political commitment, resources, guidelines, and health information systems to facilitate collaborative care [46–48]. To address these potential challenges, this study will develop a patient decision aid based on the best available evidence that can support both patients and providers in the decision-making process. In addition, with input from various stakeholders including hospital administrators, the IP-SDM care model will be integrated into the clinical practice to overcome potential organizational obstacles. Also, the cost-effectiveness of implementing the IP-SDM model will be evaluated to facilitate its future dissemination.

This study has several limitations. First, contamination can be a threat that biases the results towards null. Contamination is possible since it is not feasible to conduct a CRT design as discussed before. To identify the effects of SDM and alleviate the bias that may be introduced by contamination, this study will use randomization as the instrumental variable and examine how the assessed level of SDM after intervention would affect outcomes of interests. Second, the generalizability of this study should be interpreted with caution. The study site of this study was selected to ensure that mothers with mental health needs could access relevant services during the study. However, only a few maternal and child healthcare institutions in China have already integrated the screening and intervention for PND in routine maternal care. Thus, the findings may not be generalized to other regions of China. To maximize generalizability, this is an open-label trial with its interventions fully embedded into daily clinical practice.

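### Randomised arm is the only named instrument for shared decision-making (SDM), so the instrumental estimate credits SDM with whatever part of the package effect bypasses the measured SDM role

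*Protocol article*

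**What the plan says.** Under Statistical analysis (Evaluating the effectiveness of interventions), the protocol says that "this study will use causal mediation analysis to estimate how the levels of SDM affect multiple outcome indicators", "using whether they belong to the intervention or control group as an instrumental variable". It then allows regression models for mediation, including exposure–mediator interaction, and adds that these can be combined with instrumental variables "to analyze the mechanisms by which the levels of SDM itself contribute to multiple patient outcomes". Arm is the only instrument named.

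The limitations paragraph of the Discussion gives the instrument a second job, which is to identify SDM effects and lessen contamination bias: "this study will use randomization as the instrumental variable and examine how the assessed level of SDM after intervention would affect outcomes of interests".

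The SDM variable is an adapted Control Preference Scale which, according to Table 1, "can classify patients into three types: active decision makers, negative decision makers, and shared decision makers". The Follow-Up Survey takes it once: "measures of shared decision-making (at one month only), decisional conflict, depressive symptoms".

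The Intervention section describes a decision-aid booklet, a nurse telephone call and, for women who attend the clinic, an SDM consultation. The call includes "identifying decision problems, exchanging evidence-based information" and clarification of values. In Table 1 the first DCS dimension is "informed, i.e., the extent to which patients understand the potential benefits and risks of the options available to them"; others cover clarity of values and feeling supported. Randomization and blinding states that mothers and providers cannot be blinded.

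**The concern.** An instrument must reach the outcome only through the variable it instruments (the exclusion restriction). Here that variable is a self-reported decision role. A woman can come away from the booklet and the call better informed, clearer about her values and better supported, and so score lower on decisional conflict, while reporting the same role as before. That effect belongs to the package, not to SDM as measured.

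There is also a conflict inside the analysis. Mediation exists to divide an effect into a part through the mediator and a part around it. Using arm as the sole instrument for the mediator sets the second part to zero by assumption.

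Two claims are at stake: how SDM itself affects mental health outcomes, which the Discussion lists as the trial's first contribution, and the claim that the analysis mitigates the contamination risk of individual randomisation at a single site.

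**Working it through.** **The plan's own figure.** The Sample size section uses z values of 1.96 and 0.84 and an effect of 0.3 SD. This gives 2 × (1.96 + 0.84)² / 0.3² = 174.2, against 174 stated. Then 174 / 0.85 = 204.7, rounded to 205 per group, or 410 in total. The figure reproduces. No design figure is given for the instrumental or mediation analysis.

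**What the instrumental estimate measures.** Let d be the arm difference in the proportion with a shared role, b the effect of a shared role on the outcome, and g the effect of arm that bypasses the role.

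- Arm difference in outcome: T = b·d + g.
- Instrumental (Wald) estimate: T / d = b + g / d.
- With s = g / T, the true SDM effect is b = T(1−s) / d, so the estimate overstates b by 1/(1−s).

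**Illustration.** T = 0.3 SD is the protocol's planned effect; d = 0.20 and the values of s are assumed.

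| Share bypassing the role (s) | Instrumental estimate (SD) | True SDM effect (SD) | Overstatement |
|---|---|---|---|
| 0 | 1.50 | 1.50 | 1.00 |
| 25% | 1.50 | 1.12 | 1.33 |
| 50% | 1.50 | 0.75 | 2 |
| 75% | 1.50 | 0.37 | 4 |
| 100% | 1.50 | 0 | no SDM effect to recover |

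The second column never moves. Over assumed d from 0.10 to 0.40 the estimate runs from 3.00 to 0.75 SD, but the overstatement factor depends only on s.

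A simulation (174 per arm, 4,000 runs, an unmeasured SDM–outcome confounder, d = 0.20) gave median estimates of −1.50, −1.51 and −1.51 when the true SDM effect was −1.50, −0.75 and 0. Negative values favour the intervention. The estimator cannot tell these cases apart.

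**Strength of the instrument.** F = d² / [(p0·q0 + p1·q1) / 174], with p0 and p1 the shared-role proportions in the control and intervention arms and q = 1 − p. The control proportion is assumed to be 40%.

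| d | First-stage F |
|---|---|
| 0.10 | 3.6 |
| 0.15 | 8.0 |
| 0.20 | 14.5 |
| 0.30 | 34.8 |
| 0.40 | 69.6 |

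The instrument is weak if the package shifts reported roles only modestly.

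**Contamination.** If a fraction c of controls receives the whole package, T and d both shrink by (1−c). The ratio T / d is unchanged, so dilution is undone but the overstatement stays. If controls pick up information without a change in reported role, T shrinks and d does not, and nothing is corrected.

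**Timing.** The role and the primary DCS are taken in the same one-month survey, so the order of mediator and outcome is not established for that outcome. Decisional conflict and depressive symptoms are measured again at three and six months.

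**The case against.** The Conceptual framework draws decision support leading to SDM and SDM leading to outcomes. If every effect ran through the measured role, the estimate would be unbiased. This stands as a limit on the point: the size of the bias is unknown. But the framework does not say that other paths are absent, and the Intervention section and Table 1 together describe one. The overlap is shown for the DCS. For depressive symptoms it is less direct, though the framework itself lets affective-cognitive outcomes pass on to health outcomes.

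The protocol also allows regression-based mediation with interaction, and a full analysis plan could add sensitivity analyses. That stands too, and it makes the repair easy. It does not change the named instrument or the use made of it in the Discussion.

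Four stronger readings are tempting and are not supported:

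- *The bias exceeds the planned effect.* A direct effect of 0.1 SD with d = 0.15 gives 0.1/0.15 = 0.67 SD, which looks large beside 0.3. The scales differ. On the instrumental scale the planned effect is 0.3/0.15 = 2.0 SD, so the bias is one third of the estimate.
- *Contamination enlarges the bias.* This holds only if the direct effect stays fixed while d shrinks. With proportional dilution the bias is unchanged.
- *The instrument should instead be applied to receipt of the aid and coaching.* That leaves out the consultation, the third component, so exclusion would fail again for the same reason.
- *The trial's main result is compromised.* The mechanism analysis is an addition to the intention-to-treat comparison, which does not use the instrument.

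**Conclusion.** The point holds for the mechanism and contamination claims. On the protocol's own description the exclusion restriction is implausible, at least for decisional conflict, and it is nowhere stated or defended. The arm-instrumented estimate is the package effect rescaled by the SDM difference. It overstates the SDM effect by 1/(1−s), and the trial data cannot supply s. It does not separate direct from indirect effects, and as a contamination remedy it reaches only dilution acting through the measured role.

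The algebra assumes a linear effect, a role reduced to shared or not shared, and a direct effect in the same direction as the SDM effect. The bypass shares, the 40% control proportion and the SDM differences are illustrative assumptions. This should be fixed before the analysis, but the primary comparison, sample size and cost-effectiveness analysis do not depend on it.

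**What to change.** 1. Make the regression-based mediation the main mechanism analysis: arm as exposure, month-1 SDM role as mediator, month-3 and month-6 outcomes. Adjust for baseline DCS, decision-making preference, mental health literacy and stigma, and the screening EPDS score. Add a sensitivity analysis for unmeasured mediator–outcome confounding.
2. Keep the arm-as-instrument estimate as exploratory only. State the exclusion restriction, vary the direct effect over non-zero values, and report the first-stage F.
3. Reword the limitations paragraph to say that the instrument addresses only dilution acting through the measured SDM role, and only under that restriction.

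The cost is analysis wording; the data are already to be collected. The downside is that the mechanism result rests on confounding assumptions that can be probed but not tested, so it should be labelled exploratory.
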